## Appendix O – Co-morbidities

This is kept updated thoughout the trial but particularly at Baseline and end of study

| **Condition/Abnormality** | **Start Date** | **Stop DatE / Ongoing** | | |
| --- | --- | --- | --- | --- |
|  | ____/______/____  DD/MMM/YY | ____/______/____  DD/MMM/YY | OR |  |
|  | ____/______/____  DD/MMM/YY | ____/______/____  DD/MMM/YY | OR |  |
|  | ____/______/____  DD/MMM/YY | ____/______/____  DD/MMM/YY | OR |  |
|  | ____/______/____  DD/MMM/YY | ____/______/____  DD/MMM/YY | OR |  |
|  | ____/______/____  DD/MMM/YY | ____/______/____  DD/MMM/YY | OR |  |
|  | ____/______/____  DD/MMM/YY | ____/______/____  DD/MMM/YY | OR |  |
|  | ____/______/____  DD/MMM/YY | ____/______/____  DD/MMM/YY | OR |  |
|  | ____/______/______  DD/MMM/YY | ____/______/____  DD/MMM/YY | OR |  |
|  | ____/______/____  DD/MMM/YY | ____/______/____  DD/MMM/YY | OR |  |
|  | ____/______/____  DD/MMM/YY | ____/______/____  DD/MMM/YY | OR |  |
|  | ____/______/____  DD/MMM/YY | ____/______/____  DD/MMM/YY | OR |  |

Comments:

Study Coordinator : ______________________________

Signature: ______________________________________

## Appendix P – Concomitant Medications

From the ASK 12 Questionnaire –

Were there any issues identified in the forgetfulness or behavior sections that suggest that a webster/blister pack would be useful?  Yes  No

If yes, please add medication adherence as an issue on the care plan

| **CM #** | **Medication / Drug Name**  **(generic name preferred)** | **Start Date** | **Stop Date / Ongoing** | **Indication** | **Dose**  **(units)** | **Route*** | **Frequency**** |
| --- | --- | --- | --- | --- | --- | --- | --- |
|  |  | **____/_______/_______**  **DD / MMM / YYYY** | **____/_______/_______**  **DD / MMM / YYYY**  **Ongoing** |  |  |  |  |
|  |  | **____/_______/_______**  **DD / MMM / YYYY** | **____/_______/_______**  **DD / MMM / YYYY**  **Ongoing** |  |  |  |  |
|  |  | **____/_______/_______**  **DD / MMM / YYYY** | **____/_______/_______**  **DD / MMM / YYYY**  **Ongoing** |  |  |  |  |
|  |  | **____/_______/_______**  **DD / MMM / YYYY** | **____/_______/_______**  **DD / MMM / YYYY**  **Ongoing** |  |  |  |  |
|  |  | **____/_______/_______**  **DD / MMM / YYYY** | **____/_______/_______**  **DD / MMM / YYYY**  **Ongoing** |  |  |  |  |

***ROUTE:**  ****FREQUENCY:**

IV (intravenous) SC (subcutaneous) QD: once daily BID: twice a day

PR (per rectum) INH (inhaled) TID: three times a day QID: four times a day

IM (intramuscular) TD (transdermal) PRN: as occasion requires single dose

SL (sublingual) TOP (topic al) Every morning Every evening

PO (per os – by mouth) Every other hour Other, specify

Others, specify-----------

## Appendix Q – End of Study Assessment Form

**To be completed on all patients (Intervention AND Control)**

| **Outcomes** | | **Yes** | **No** |
| --- | --- | --- | --- |
| 1 | Patient has **completed** the study (if yes complete table below)  Date of End of Study ____ / ____ / ______ |  |  |
| 2 | Patient has **DIED**  Date of Death ____ / ____ / ______ |  |  |
| 3 | Patient has been placed on the **transplant waiting list** (Complete below when placed on list)  Date of placement on waiting list ____ / ____ / ______ |  |  |
| 4 | Patient has been **LOST** to follow up  Date of last contact ____ / ____ / ______ |  |  |
| 5 | Date of Palliative Care Referral ____ / ____ / ______ |  |  |

**If patient completed the study please ensure the following:**

| ***End of Study Activities*** | | **Yes** | **No** |
| --- | --- | --- | --- |
| 1 | CLDQ completed by patient |  |  |
| 2 | EQ5D 5L completed by patient |  |  |
| 3 | Cirrhosis Knowledge Assessment Questionnaire completed by patient |  |  |
| 4 | PIH completed by patient |  |  |
| 5 | ASK-12 completed by patient |  |  |
| 6 | Resource Use Questionnaire completed by patient |  |  |
| 7 | Patient satisfaction survey completed by patient |  |  |
| 8 | MELD and Child Pugh Scores completed? |  |  |
| 9 | Concomitant medications recorded? |  |  |
| 10 | Hospital Admissions form completed? |  |  |
| 11 | Outpatient appointments form completed? |  |  |
| 12 | Nursing Contacts page completed? |  |  |
| 13 | All assessment forms completed (Appendix C, D, E, F, G, R) |  |  |

Study Coordinator : ______________________________

Signature: ______________________________________

Date: _________________________

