## Secondary Objectives

- To evaluate incremental cost effectiveness for this intervention, relative to usual care. Assessment of quality of life will be a necessary component of the economic analysis. The QALY will be used to assess this outcome.
- To evaluate the effect of CDM on mortality
- To evaluate the effect of CDM on the quality of care provided to patients in the intervention arm. This will be assessed using the following measures:
  - attendance at planned outpatient care;
  - medication adherence;
  - adherence to antibiotic prophylaxis protocols for patients with ascites;
  - adherence to variceal bleeding prevention protocols;
  - adherence and response to alcohol abuse treatment protocols in alcoholic liver disease patients; and
  - referral rates to liver transplantation assessment teams.
- To compare self-management ability and knowledge of patients in the CDM arm with usual care models.

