## End of Study

Patients will have an end of study visit at withdrawal, when listed on the transplant waiting list, or at the end of the study (24 months after the randomisation of the first patient).

Both groups will have the following collected:

- Cirrhosis Knowledge Assessment Questionnaire
- Ask 12
- CLDQ
- EQ-5L-5D
- PIH Scale
- Patient Satisfaction Questionnaire
- Resource use questionnaire
- MBS and PBS information (to be collected centrally by the coordinating site) if the patient signed the consent form at the beginning of the trial.

Please remind the participant that a member of the study coordinator team may be in contact via telephone to ask a few questions about their experiences but they can refuse to participate if they wish. Thirty two patients will be consecutively recruited (8 patients per site, 4 patients from each study arm) for the telephone interviews.

The following will also be completed/updated at end of study in both groups:

- Hospital admissions log
- Outpatient attendance log
- Concomitant medications
- Comorbidities list
- Child Pugh & MELD score
- HCC assessment
- Ascites and HE assessment
- Osteoporosis assessment
- Alcohol assessment
- Variceal assessment
- Nutrition assessment

It is preferable that the information is collected face-to-face as the control group patients can have some education about their liver disease if they wish. Ensure they receive the Cirrhosis Booklet.

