## Intervention period

Patient recruitment will occur during a 12-18 month window and the intervention will occur for 24 months for each patient. In the case of patient death, liver transplantation and loss to follow up, the study will end.

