## Statistical methods

All analyses will be performed according to an intention-to-treat protocol. Differences between groups for hospitalization rates, quality indicators, satisfaction rates and self-management scores will be assessed using negative binomial regression, which is appropriate for count data with evidence of over-dispersion. All models will allow adjustment for baseline values and other co-variates. Suitable transformations will be applied in the case of non-normally distributed data.

For the economic analysis mean costs between the intervention and control groups will be compared and incremental cost effectiveness ratios presented with confidence intervals. Cost effectiveness acceptability curves for varying threshold values of cost effectiveness will also be presented ([46](#_ENREF_46)). An assessment of the sensitivity of the results obtained to variation in measured resource use, effectiveness and/or unit costs will be undertaken using appropriate one-way and multi-way sensitivity analysis ([47](#_ENREF_47)). Differences between groups in quality of life scores will be assessed using mixed effects regression to account for the repeated measures (every 3 months) and subsequent within-Participant correlation. Survival analysis will be performed using Cox regression with results presented as Kaplan-Meir survival curves.

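### Appendix Q ties the hospital admissions log to study completers, no section secures it for patients who die or are lost, and the protocol names different events that end data collection

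*Protocol*

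**What the plan says.** - **When admissions are logged.** The visit section for Months 3 to 18 and both activity schedules place the admissions record at Month 12 and at end of study. The log itself (Appendix J) takes the reason for admission from the discharge summary. It offers two review periods: randomisation to 12 months, and 12 months to trial end.
- **Appendix Q, outcome rows.** The form is for all patients in both arms. The row for completing the study says "if yes complete table below". The rows for death and for loss to follow-up ask only for a date. The waiting-list row says "Complete below when placed on list". There is no row for withdrawal.
- **Appendix Q, activities table.** It is headed "If patient completed the study please ensure the following". One of its 13 items is "Hospital Admissions form completed".
- **End of Study section.** "Patients will have an end of study visit at withdrawal, when listed on the transplant waiting list, or at the end of the study". The hospital admissions log is among the items then brought up to date in both groups, with no condition that the patient completed.
- **Intervention period section.** "In the case of patient death, liver transplantation and loss to follow up, the study will end".
- **Statistical methods section.** "All analyses will be performed according to an intention-to-treat protocol".

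**The concern.** The primary outcome is a count of admissions, and an admission that nobody writes down cannot be recovered by any analysis. Appendix Q is the form that closes a patient's participation. Read literally, it asks for the log only when the patient completed. The End of Study section corrects this for withdrawal and listing but does not mention death or loss. A site that follows both texts as written has no instruction to log the admissions of a patient who dies in month 9, and none to log the second year of a patient who dies in month 18.

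Patients who die are likely to be among those admitted most often, and the Background expects many deaths in this population. A second gap concerns what happens after exit: collection stops at listing or withdrawal under End of Study but at transplantation under Intervention period. Under the first rule, admissions after listing or withdrawal are not collected, although all analyses are said to follow intention to treat.

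**Working it through.** **1. The passages side by side**

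| How the patient leaves | End of Study section | Appendix Q | Intervention period section |
|---|---|---|---|
| Completes | log required | log required | - |
| Withdraws | visit and log required | no row | not named |
| Listed for transplant | visit and log required | row present, instruction unclear | names transplantation, not listing |
| Dies | not named | date only | study ends |
| Lost to follow-up | not named | date of last contact only | study ends |

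No section explicitly secures the log in the last two rows. The first three rows show that Appendix Q is narrower than End of Study, and that the event ending collection differs.

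**2. Scale of the loss from deaths**

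The protocol gives no figure for this loss, so there is none to reproduce.

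Inputs from the protocol:
- 3 admissions per person-year in usual care and a rate ratio of 0.80 (Sample size section)
- two-year survival of 60% for Child Pugh B and 35% for Child Pugh C (Background)
- 80% survival if the whole 20% attrition allowance (Sample size section) is death
- mortality hazard ratio 0.6 from the pilot (Background; 95% CI 0.3 to 1.5, P=0.32)

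Assumptions:
- a gamma frailty g with mean 1 and variance v of 0.5 or 1 multiplies both the admission rate and the death hazard
- no log exists for the 12-month period in which a patient dies, so logged time is 0, 1 or 2 years
- unlogged time leaves both numerator and denominator
- the rate is total admissions over total person-time

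Formulas, with baseline death hazard h and S2 the two-year survival:
- h = (S2^(-v) - 1)/(2v)
- A(t) = (1 + v·h·t)^(-1/v), the proportion alive at t
- B(t) = (1 + v·h·t)^(-1/v - 1), the mean of g counted over those alive at t
- admissions that occur are proportional to the integral of B from 0 to 2, which is (1 - A(2))/h
- admissions logged are proportional to B(1) + B(2)
- person-time is the integral of A from 0 to 2; logged person-time is A(1) + A(2)

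Worked case, S2 = 0.60 and v = 1:
- Control: h = (1/0.6 - 1)/2 = 0.333. Occurring: 0.4/0.333 = 1.200, or 3.6 admissions per patient. Logged: 0.75² + 0.60² = 0.9225. Unlogged: 1 - 0.9225/1.200 = 23.1%. Person-time: ln(1.667)/0.333 = 1.5325 years; logged: 0.75 + 0.60 = 1.35.
- Intervention with hazard ratio 0.6: h = 0.2, A(1) = 0.8333, A(2) = 0.7143. Occurring: 0.2857/0.2 = 1.4286. Person-time: ln(1.4)/0.2 = 1.6824. Logged: 0.6944 + 0.5102 = 1.2046; logged person-time: 1.5476.
- Rate ratio with full logs: 0.8 × (1.4286/1.6824)/(1.200/1.5325) = 0.868.
- Rate ratio as logged: 0.8 × (1.2046/1.5476)/(0.9225/1.35) = 0.911.

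| Two-year survival | v | Control admissions unlogged | Rate ratio, full logs | Rate ratio, as logged | Added by missing logs |
|---|---|---|---|---|---|
| 80% | 0.5 | 8.1% | 0.817 | 0.826 | 0.01 |
| 80% | 1 | 10.6% | 0.833 | 0.851 | 0.02 |
| 60% | 0.5 | 17.8% | 0.835 | 0.856 | 0.02 |
| 60% | 1 | 23.1% | 0.868 | 0.911 | 0.04 |
| 35% | 0.5 | 34.4% | 0.858 | 0.908 | 0.05 |
| 35% | 1 | 44.1% | 0.909 | 1.013 | 0.10 |

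If mortality is equal between arms, the terms in h cancel and both ratios are exactly 0.80 in every row. The loss is then one of events only.

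Without frailty, the share of admissions lost equals the share of person-time lost. At 60% survival h = -ln(0.6)/2 = 0.2554, person-time is 0.4/0.2554 = 1.566 years, logged time is 0.7746 + 0.60 = 1.3746, and 12% is lost. The same sum gives about 6% at 80% survival (5.5% before rounding) and 24% at 35%.

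**The case against.** The strongest reply is that Appendix Q is a closing checklist and not the collection rule. Seven of its 13 items are questionnaires that the patient fills in, which explains a heading addressed to completers. The rule is in End of Study, which has no completer condition and covers withdrawal and listing. Intervention period can be read as making death and loss ends of study, which would bring the log with them. Appendix J works from discharge summaries and needs no living patient. Outcome data are monitored every three months, and centralised costing data on public inpatient episodes are to be obtained with consent.

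Much of this stands. A reader might infer that the primary outcome is lost for everyone who leaves early. The documents do not support that, because the log up to exit is required at withdrawal and at listing in both arms. For deaths and losses, though, the reply needs two sections to be combined by inference while the form signals the opposite. Neither the monitoring nor the costing data is named as a substitute for the log.

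A reader might also infer that the effect estimate is badly biased. That needs mortality to differ between arms, and the pilot hazard ratio was not significant. Part of the drift from 0.80 is survivorship that complete logs would leave in place. The ratio of 1.01 needs Child Pugh C survival in every patient and frailty variance 1, although patients expected to survive under three months are excluded and the protocol plans for less severe liver failure than in the pilot.

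Nor is it established that listing is driven by treatment. The outcome named in Secondary Objectives is "referral rates to liver transplantation assessment teams"; listing is a later and separate decision, and the protocol gives no listing rates by arm.

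**Conclusion.** The point holds as a contradiction and a gap. Appendix Q is narrower than End of Study on who needs the admissions log. No section explicitly secures it for patients who die or are lost. The event that ends collection is listing or withdrawal in one place and transplantation in another, which sits poorly with the intention-to-treat statement.

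If sites follow the form, about 8-11% of control admissions go unlogged at 80% two-year survival and 18-23% at 60%. The 34-44% at 35% survival is an extreme. With equal mortality there is no bias. With a mortality hazard ratio of 0.6 the missing logs add about 0.01-0.02 to the rate ratio at 80% survival and 0.02-0.04 at 60%, on top of a survivorship shift that full logs do not remove.

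These figures rest on the assumed frailty, on there being no log for the period of death, and on a simple rate ratio; a negative binomial fit may weight patients differently. Losses to follow-up and admissions after listing or withdrawal are not in the figures. The point matters because the lost events belong to the primary outcome and cannot be recovered at analysis.

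**What to change.** - In Appendix Q and End of Study, require the admissions log for every randomised patient whatever the reason for leaving, completed from hospital records from randomisation to death or the planned 24 months. Take the log item out of the completers' table, add a withdrawal row to Appendix Q, and let the Appendix J review periods end at an exit date.
- Continue records-based collection of admissions and the death-registry check after listing and after withdrawal from the intervention, unless the patient withdraws consent to records access.
- Reconcile End of Study, Intervention period and Appendix Q so that they name one data end-point. This should also settle the planned end itself, which End of Study counts from the first patient randomised and Intervention period counts for each patient.

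The cost is a change of wording and forms, plus modest extra chart abstraction for patients who die, are listed, withdraw or are lost. The hospital records and the death registry are already in use in the trial.

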## Appendix R – HCC Assessment form

**Timepoint Ax COMPLETED:**  Baseline (intervention only) - Date: ____ / ____/ _____

End of Trial - Date: ____ / ____/ _____

| ***HCC*** | | **Yes** | **No** |
| --- | --- | --- | --- |
| 1 | Has the patient had an upper abdominal ultrasound? (if no, add to care plan to refer for screening) |  |  |
| 2 | How many ultrasounds has the patient had the last 2 years  0  1 Date : ____ / ____/ _____  2 Date : ____ / ____/ _____  3 Date : ____ / ____/ _____  4 Date : ____ / ____/ _____  N/A – patient only just diagnosed with cirrhosis (baseline only option) |  |  |
| 3 | Was HCC found in any of the above ultrasounds? |  |  |

Comments:

## Appendix S – Care Plan

**ALFIE TRIAL CARE PLAN**

| Date: | Date of randomization: ___ / ___ / _____ | |  |
| --- | --- | --- | --- |
| Aetiology : | Childs Pugh: MELD: | Consultant: | |
| **Active Problem list:** | **Actions / Plan** | | **Date resolved** |
| **#** |  | |  |
| **#** |  | |  |
| **#** |  | |  |
| **#** |  | |  |
| **#** |  | |  |
| **#** |  | |  |
| **#** |  | |  |
| **#** |  | |  |
| **#** |  | |  |
| **#** |  | |  |
| **#** |  | |  |
| **Comment/ Consultant instructions:**  **Signature: ……………………………………………………..Date:…………………………………** | | | |

Not for filing in MR

ALFIE TRIAL

**CARE PLAN REVIEW DATES**

Please document when the care plan was discussed/reviewed with the treating Specialist and ask the Specialist to sign below:

Review Date: ____________ Signed: _______________________ Name: ___________________________

Review Date: ____________ Signed: _______________________ Name: ___________________________

Review Date: ____________ Signed: _______________________ Name: ___________________________

Review Date: ____________ Signed: _______________________ Name: ___________________________

Review Date: ____________ Signed: _______________________ Name: ___________________________

Review Date: ____________ Signed: _______________________ Name: ___________________________

Review Date: ____________ Signed: _______________________ Name: ___________________________

Review Date: ____________ Signed: _______________________ Name: ___________________________

Review Date: ____________ Signed: _______________________ Name: ___________________________

Review Date: ____________ Signed: _______________________ Name: ___________________________

Review Date: ____________ Signed: _______________________ Name: ___________________________

Review Date: ____________ Signed: _______________________ Name: ___________________________

Review Date: ____________ Signed: _______________________ Name: ___________________________

Review Date: ____________ Signed: _______________________ Name: ___________________________

Review Date: ____________ Signed: _______________________ Name: ___________________________

Review Date: ____________ Signed: _______________________ Name: ___________________________

Review Date: ____________ Signed: _______________________ Name: ___________________________

Review Date: ____________ Signed: _______________________ Name: ___________________________

## Appendix T – Charlson Comorbidity index

| **Charlson Comorbidity Index** | **ALFIE** | **Subject**  **ID** | **Subject Initials** |
| --- | --- | --- | --- |
|  |  | __- __ __ __ | __ __ __ |

1. **Has the patient had a myocardial infarction? (MI)**

- Yes
- No

*Criteria: Myocardial infarction includes patients with one or more definite or probably myocardial infarction. These patients should have been hospitalised for chest pain or an equivalent clinical event and have electrocardiographic and/or enzyme changes. Patients with electrocardiographic changes alone who have no clinical history are not designated as having an infarction.*

**2. Has the patient been hopsitalised or treated for heart failure? (CHF)**

- Yes
- No

*Criteria: Congestive heart failure includes patients who have had exertional or paroxysmal nocturnal dyspnoea and who have responded symptomatically (or on physical examination) to digitalis, diuretics, or afterload reducing agents. It does not include patients who are on one of those medications but who have had no response and no evidence of improvement of physical signs with treatment.*

**3. Does the patient have peripheral vascular disease? (PVD)**

- Yes
- No

*Criteria: Peripheral vascular includes patients with intermittent claudication or those who had a bypass for arterial insufficiency, those with gangrene or acute arterial insufficiency, and those with a treated or untreated thoracic or abdominal aneurysm (6cm or more).*

**4. Has the patient had a CVA or transient ischaemic disease? (CVA)**

- Yes
- No

*Criteria: Cerebrovascular disease includes patients with a history of a cerebrovascular accident with minor or no residual, and patient who have had transient ischaemic attacks. If the CVA resulted in hemiplegia, code only hemiplegia.*

**5. Does the patient have hemiplegia? (PLEGIA)**

- Yes
- No

*Criteria: This includes patients with a hemiplegia or paraplegia, whether it occureed as a result of a cerebrovascular accident or other condition.*

**6. Does the patient have asthma, chronic lung disease, chronic bronchitis or emphysema? (COPD)**

- Yes
- No

*Criteria: Pulmonary disease includes patients with asthma, chronic bronchitis, emphysema, and other chronic lung disease who have ongoing symptoms such as dyspnoea or cough, with mild or moederate activity. This includes patients who are dyspnoeic with slight activity, with or without treatment and those who are dyspnoeic with moderate activity despite treatment, as well as patients who are dyspnoeic at rest, despite treatment, those who require constant oxygen, those with CO2 retention and those with a baseline PO2 below 50 torr.*

